## **LIST OF ABBREVIATIONS**

ANCOVA: Analysis of covariance

CTCAE: Common terminology criteria for adverse events

EQ-5D-5L: EuroQoL health status measure, 5 dimensions, 5 levels

FES-I: Falls Efficacy Scale – International

ICC: Intraclass correlation coefficient

Mini-BEST: Mini Balance Evaluation Systems Test

RBT: Reactive balance training

## 1. INTRODUCTION

### 1.1 Background and rationale

Remaining active after stroke is essential to recovery, maintaining quality of life, and reducing secondary stroke risk. However, impaired balance control post-stroke increases fall risk, contributes to fear of falling, and reduces overall mobility, activity, and community integration. Therefore, effective interventions to improve balance control and reduce fall risk are essential to ongoing recovery and quality of life post-stroke. However, while there is unequivocal evidence that exercise, specifically balance training, is the most effective intervention for preventing falls in older adults without stroke, it is unclear if exercise prevents falls after stroke.

Effective balance reactions (e.g., reactive stepping) are essential to avoid falling following a loss of balance, or balance perturbation. Reactive balance training (RBT), where clients experience repeated balance perturbations, is a novel type of exercise that aims to improve control of balance reactions. We found that RBT improves reactive stepping ability in people with stroke. Our recent meta-analysis found that RBT reduces rate of falls in daily life by ~40% among older adults and people with neurologic conditions, including stroke.

Clinicians are unsure how to optimally prescribe RBT. Exercise is often prescribed considering frequency, intensity, time, and type; these parameters are interdependent. For example, as intensity increases, frequency or time can decrease to achieve similar benefits. Clinicians report that limited time in rehabilitation services and competing rehabilitation goals and priorities mean that there is little time available to include RBT in a client's treatment plan. Therefore, it would be valuable to know if a short duration of high-intensity RBT can improve reactive balance control post-stroke. However, it is possible that people with stroke would not tolerate high intensity perturbations and, therefore, require lower-intensity but long-duration RBT. No study has directly compared different RBT training intensities among people with stroke.

### 1.2 Objectives and hypotheses

The purpose of this study is to determine the optimal intensity of RBT post-stroke. The 'optimal' intensity is the intensity that improves reactive balance control in fewer sessions, without any apparent negative consequences (i.e., no increase in adverse outcomes). We expect that high-intensity training (50% above the multi-step threshold) will improve reactive stepping ability faster than moderate-intensity training (at the multi-step threshold). If the first reactive step is not effective in avoiding a fall after a loss of balance, additional steps must be taken; therefore, the number of steps needed to recover from a loss of balance is a global indicator of the effectiveness of balance reactions. We will assess reactions to novel, untrained, balance perturbations throughout training, and calculate the rate of decline in average number of steps taken to recover balance (i.e., learning rate). Retention of learning will be assessed one week post-training. Our primary hypotheses are:

- 1) Adaptation rate will be faster for high-intensity RBT than moderate-intensity RBT;
- 2) Adaptation rate will be faster for both RBT groups than a walking control group; and
- 3) Both RBT groups will have better retention of learning than the walking control group; i.e., the RBT groups will take fewer steps to respond to the novel perturbation than the walking control group one week post-training.

Secondary objectives are to compare the rate of adverse outcomes between groups, and to determine the effect of different intensities of RBT on the mechanisms underlying improved reactive stepping ability, functional balance, falls efficacy, and participation in daily activities.

## 2. METHODS TO BE USED

### 2.1 Trial design

This study is an outcome-adjudicator blinded randomized controlled trial, following motor learning protocols (Figure 1). People with chronic stroke (n=63) will be randomly assigned to: 1) high-

intensity RBT, 2) moderate-intensity RBT, or 3) a walking control group. Training sessions will take place on four consecutive days; reactive stepping will be assessed pre-training, at the end of each training session (to determine the rate of adaptation), and after a delay of one week (to determine retention of learning effects) using a novel untrained perturbation. Falls in daily life, physical activity, and participation will be assessed for 12 months post-training.

| Baseline
Day 1                                                                                                   | Training sessions
Days 2-5                                                                                                                                                              | Retention
Day 12                                                   | Falls monitoring
0-12 months post-training | Follow-up
12 months post-training |
|----------------------------------------------------------------------------------------------------------------------------|---------------------------------------------------------------------------------------------------------------------------------------------------------------------------------------------------|------------------------------------------------------------------------------|------------------------------------------------------|---------------------------------------------|
| Multi-step threshold
3 backward-fall perturbations
Mini-BEST, FES-I, EQ-5D-5L, fear of falling
Cohort descriptors | 
High-intensity RBT
3 backward-fall perturbations
 
Moderate-intensity RBT
3 backward-fall perturbations
 
Walking practice
3 backward-fall perturbations
 | 3 backward-fall perturbations
Mini-BEST, FES-I, EQ-5D-5L, fear of falling | Falls in daily life                                  | FES-I, EQ-5D-5L, fear of falling            |

**Figure 1: Overview of the trial design.** Mini-BEST=mini-Balance Evaluation Systems Test; FES-I=Falls Efficacy Scale-International; EQ-5D-5L=EuroQoL 5-level quality of life measure; RBT=reactive balance training

## 2.2 Trial interventions

Training sessions will be overseen by a physiotherapist and will last for 1 hour over 4 consecutive days. Training will occur using the ‘FallsLab’ custom-built 6m x 3m motion platform (Figure 2). A robotic safety harness gantry allows participants to move freely on the platform, but prevents falls if they are unable to regain balance. An accelerometer (Series 7523A, Dynamic Transducers and Systems, Chatsworth, California, USA) placed on the platform records platform acceleration. Eight high-resolution video cameras will be positioned around the room to collect markerless 3-dimensional kinematic data (Theia Markerless, Inc., Kingston, ON). Four force plates on the platform (1.5m x 1.5m, model BP11971197-2000, Advanced Mechanical Technology, Inc., Watertown, Massachusetts, USA) record forces and moments in 3 dimensions.

A baseline data collection session will be completed before the first training session. The forward multi-step threshold will be determined, using a staircase procedure. Participants will initially experience a backward-directed platform perturbation (causing a forward ‘fall’) at 0.5 m/s peak acceleration (intensity). Participants will be instructed to do whatever they need to do to recover balance but, if they need to take a step, to minimize the number of steps taken. If participants do not step or only take a single step to recover balance, the intensity will be increased in 0.5 m/s increments until the participant needs to execute a multi-step reaction to recover balance. The intensity will then be reduced in 0.25 m/s increments until the participant only takes one step (first reversal). The intensity will be increased, and then decreased, in 0.25 m/s increments, reversing when the participant’s step response changes (i.e., single- or multi-step reaction) until there are four reversals (Figure 3). The multi-step threshold is the highest perturbation magnitude where the participant can recover balance with a single step. The multi-step threshold should be around 2-3 m/s, which will take approximately 10-16 trials to determine.

Participants assigned to the RBT groups will experience 36 multi-directional (left-, right-, and forward-fall) perturbations in each training session, presented in an unpredictable sequence. Participants assigned to **high-intensity RBT** will experience perturbations at 150% of the multi-step threshold; for example, for a multi-step threshold of 2 m/s the high intensity will be 3 m/s.

[figure not shown]

**Figure 2: FallsLab motion platform and apparatus.**

Participants assigned to the **moderate-intensity RBT** group will experience perturbations at the multi-step threshold. If participants respond to the perturbations with a single step (high intensity group) or no step (moderate intensity group) in >50% of trials, the intensity will be increased by 25% in the subsequent training session. Participants in the **walking control** group will complete 36 unperturbed walking trials on the FallsLab platform in each training session.

[figure not shown]

**Figure 3: Example of the staircase procedure to determine the multi-step threshold.** The first multi-step reaction is observed at 2.5m/s, at which point the intensity (peak acceleration) is reduced until a single step is observed. The perturbations are increased and decreased in 0.25m/s increments until there are four reversals of the ‘staircase’.

### 2.3 Group allocation and blinding

Participants will be assigned using blocked (block size 6 or 9) randomization (computer-generated random sequence), stratified by sex to one of the three training groups. Participants cannot be blinded to group allocation for exercise trials. The primary outcome will be obtained during the training sessions and will be scored by a blinded adjudicator from raw data (videos). Secondary outcomes will be obtained by a blinded research assistant. To maintain allocation concealment, group allocation will be performed centrally by the principal investigator, who will not be involved in recruiting.

### 2.4 Participants

Community-dwelling men and women (>20 years old) with chronic stroke (>6 months post-stroke) will be recruited. Participants will be excluded if they:

- Are unable to stand independently without upper-limb support for >30 seconds and/or walk independently (without a gait aid) for ≥10 metres;
- Have another neurological condition that could affect balance control (e.g., Parkinson’s disease);
- Have cognitive impairment (Montreal Cognitive Assessment score <26), or severe language or communication difficulties affecting understanding instructions;
- Have contraindications to RBT, such as osteoporosis, activity restrictions due to cardiac event/surgery, or severe spasticity in the lower extremity; and/or
- Are currently attending in- or out-patient physiotherapy or supervised exercise.

Several strategies will be used to identify participants: 1) placing advertisements in the community (e.g., in health centres, local newspapers, or online; Appendix A); 2) requesting referrals from existing stroke rehabilitation programs at Toronto Rehab; and 3) Epic. For individuals responding to advertisements, the volunteer will be invited to contact the research team. For patients referred by healthcare providers at Toronto Rehab, initial contact may be made by a member of the research team (with the volunteer’s consent) or the volunteer may choose to contact the research team. The healthcare provider may provide these patients with a study brochure (Appendix B) to give them some information about the study and help them to decide if they want to hear more. We will follow UHN guidance regarding identifying potential participants using Epic. To identify patients who are about to be discharged from rehabilitation and may be interested in participating in research, members of the research team will view the stroke in-patient and out-patient rehab program treatment schedules for patients that have indicated “Yes” to the “RSH (research) OK to contact” field in Epic. To identify patients with more chronic strokes, we will also submit a Data and Reporting Request for identifiers for UHN patients with a history of stroke that have indicated “Yes” to the “RSH (research) OK to contact” field in Epic. We will review patients’ charts to pre-screen them using the criteria above. Eligible

patients will be contacted by the research team using the patients' preferred contact method, as indicated in Epic (Appendix L).

## 2.5 Outcome measures

Outcome assessment will be repeated one week after the end of the training program to assess retention of training effects. Falls will be assessed for 12 months post-training.

### 2.8.1 Primary outcome: balance reactions to an untrained perturbation

Responses to backward-fall perturbations will be assessed at the end of each session, and at the one-week retention time-point. An untrained perturbation (i.e., backward-fall perturbation) will be used to test transfer of learning to a novel context. To prevent participants from pre-planning their responses, the backward-fall perturbations will be completed in block of trials with 6 low-magnitude forward-fall and lateral perturbations (25-50% of participants' multi-step threshold), presented in an unpredictable sequence. Improved reactive stepping with practice of forward-fall perturbations transfers to reactions to backward-fall perturbations in people with chronic stroke. Participants will experience 3 forward-directed platform translations, evoking a backward loss of balance, at the multi-step threshold. Because backward falls are more challenging than forward or lateral falls, a backward-fall perturbation at the forward-fall multi-step threshold should evoke a multi-step reaction, at least prior to training. Testing at each participant's multi-step threshold ensures that participants will initially experience challenges responding to the perturbation and there is room for improvement with training. The primary outcome will be number of steps taken to recover balance. Extra steps are required when the first step is ineffective for regaining balance; less effective initial steps require more extra steps. Multi-step reactions are associated with increased risk of falls in daily life, and people reduce the number of steps taken to recover balance after RBT. Therefore, number of steps taken to recover balance is a global indicator of effectiveness of balance reactions.

We will calculate the learning rate for each participant by fitting an exponential function,  $a + b \left( e^{-\frac{t}{x}} \right)$ , to their data (average number of steps taken at each assessment time point), where  $a$  and  $b$  are constants,  $t$  is the assessment time point, and  $x$  is the learning rate. Figure 4 illustrates possible results for the three groups, using three different learning curves ( $x=0.4$ , 2 and 10 for the high-intensity, moderate-intensity, and walking control groups, respectively).

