## 2.6 Sample size justification

Our primary outcome is learning rate. The sample size for each group was estimated as  $\lambda/\Delta$ , where  $\lambda$  was obtained from tables for 3 groups using probability of a Type 1 error ( $\alpha$ ) of 0.05, probability of a Type II error ( $\beta$ ) of 0.2; therefore,  $\lambda$  of 9.64 was used. Additionally:

$$\Delta = \frac{1}{\sigma^2} \sum_{i=1}^k (\mu_i - \bar{\mu})^2$$

where  $\sigma$  is the standard deviation,  $k$  is the number of groups (3),  $\mu_i$  is the mean for each groups and  $\bar{\mu}$  is the mean for all groups combined. From pilot data, we estimate a standard deviation of 9.7 for the learning rate. People with stroke typically require 3-4 steps to regain stability following the perturbation magnitudes used in the proposed study. Due to the mechanical challenges of the perturbation, at minimum 1 step is required to respond to the perturbation (i.e., young healthy adults would take 1 step to respond to the perturbation). Therefore, an improvement from 3-4 steps pre-training to 1-2 steps post-training is considered clinically meaningful, and a much larger effect size would likely not be possible. From previous studies an improvement from taking, on average, 3-4 steps pre-training to 1-2 steps post-training is feasible. Simulating learning rates between these data points (Figure 5), we expect that learning rates of approximately 0.4 ( $\mu_1$ ), 2 ( $\mu_2$ ) and 10 ( $\mu_3$ ) for the high-intensity, moderate-intensity, and walking control groups, respectively, would show meaningful differences between the three groups. Therefore,  $\Delta$  was calculated as 0.56, giving a target sample size of 17 per group or 51 participants total. To account for a ~20% rate of withdrawal, we will aim to recruit 21 participants per group, or 63 participants total. Enrolment will stop when 51 participants have completed the retention test, or 63 participants have been enrolled, whichever happens first.

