## 2.7 Analyses

One-way analysis of covariance (ANCOVA), with sex as a covariate, will be used to compare learning rates between the 3 groups. ANCOVA, controlling for the pre-training value, will be used to compare the following outcomes between the 3 groups at the post-training and retention time points: average number of steps, step initiation time, step execution time, step length, braking impulse, margin of stability, mini-BEST, and FES-I. Pre-planned contrasts will be used to compare outcomes between the high- and moderate-intensity groups, and between the two RBT groups combined and the walking control group. Alpha will be 0.05 for the primary outcome (learning rates), and adjusted for multiple comparisons using the Holm-Bonferroni method for secondary outcomes. Falls and quality of life data will be reported without inference so that these data can be used in meta-analyses and/or as pilot data for future studies.

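### A learning rate cannot be estimated after one session and is at best an exact fit after two, so the primary comparison tends to leave out early stoppers, possibly unequally by group

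*Protocol*

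**What the plan says.** Section 2.8.1 defines the endpoint: "We will calculate the learning rate for each participant by fitting an exponential function". The function is a + b·exp(−t/x), the data are the "average number of steps taken at each assessment time point", and x is the learning rate. It works as a time constant, so a small x means fast adaptation. Each average comes from few trials: "Participants will experience 3 forward-directed platform translations, evoking a backward loss of balance, at the multi-step threshold".

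Section 2.1 places these tests before training, after each of the four sessions, and one week later. Section 2.8.1 does not say whether the baseline or the retention test enters the fit.

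Section 2.7 gives the analysis: "One-way analysis of covariance (ANCOVA), with sex as a covariate, will be used to compare learning rates between the 3 groups". Each person contributes one x. The protocol has no rule for a participant whose curve cannot be fitted.

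On early stopping, section 1.1 says "it is possible that people with stroke would not tolerate high intensity perturbations". Section 2.8.2 allows withdrawal from the study depending on how severe an adverse outcome is, and lets the physiotherapist modify training for milder ones. Section 2.6 enlarges the sample "To account for a ~20% rate of withdrawal" and lets enrolment end once 51 people have completed the retention test.

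**The concern.** The endpoint needs three quantities estimated from each person's own data, and the data arrive at one point per session. Whether a participant has an endpoint at all therefore depends on how many sessions they complete, which happens after randomisation and may depend on the assigned group. An early stopper has step counts on record but no usable x to put into the ANCOVA.

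Hypothesis 1, high against moderate intensity, is the most exposed, because tolerance is the property on which those two groups might differ. If people leave the comparison at different rates, or for different reasons, the groups compared are no longer the groups randomised.

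**Working it through.** **1. The plan's own figure.** Inputs from section 2.6: means 0.4, 2 and 10, SD 9.7, λ = 9.64.

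- Overall mean = (0.4 + 2 + 10)/3 = 4.133.
- Δ = (3.733² + 2.133² + 5.867²)/9.7² = 52.91/94.09 = 0.562. The plan states 0.56.
- n = 9.64/0.562 = 17.1 per group. The plan states 17.
- The target of 51 out of 63 leaves room for 12 people (19%) without a retention test.

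The figure reproduces, apart from rounding down. The sample size is not the problem. With these means and SD, noncentral F power is 0.77 at 17/17/17. It is also 0.77 if all 12 losses fall in the high-intensity group (9/21/21). The issue is selection, not power.

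**2. Points against parameters.** The curve has three unknowns: a, b and x.

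| Last session completed | Points with baseline | Residual df | Points without baseline |
|---|---|---|---|
| 1 | 2 | −1: x not identified | 1 |
| 2 | 3 | 0: exact fit at best | 2 |
| 3 | 4 | 1 | 3 |
| 4 | 5 | 2 | 4 |

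A retention test, if attended and fitted, would add one point. A one-session participant would then also have an exact fit at best.

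**3. Two points.** Take illustrative averages of 3.67 at t = 0 and 2.67 at t = 1, a drop of one step. Any x fits exactly, with b = 1/(1 − exp(−1/x)) and a = 3.67 − b:

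- x = 0.4: b = 1.09, a = 2.58
- x = 2: b = 2.54, a = 1.13
- x = 10: b = 10.51, a = −6.84

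The last curve has an impossible plateau and could be ruled out by a constraint. The first two both level off above one step, and they carry the planned high- and moderate-intensity values. These data cannot separate the two.

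**4. Three points.** With averages y0, y1 and y2 at t = 0, 1 and 2, y0 − y1 = b(1 − r) and y1 − y2 = b·r(1 − r), where r = exp(−1/x). So r = (y1 − y2)/(y0 − y1) and x = −1/ln r. A finite positive x exists only if r lies between 0 and 1, that is, if the second change has the same direction as the first and is smaller.

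- 3.67, 2.67, 2.33: r = 0.33/1.00 = 1/3, so x = 1/ln 3 = 0.91.
- 3.67, 2.67, 1.67: r = 1, so no finite x, although this person improved by two steps.

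**5. How often a three-point solution exists.** This needs assumptions that the protocol does not give: a = 1.5, b = 2, per-trial SD of 0.5 to 1.0 steps, and averages of three whole-number counts. In simulation an exact solution existed for 34–45% of participants at x = 0.4, 21–32% at x = 2 and 5–8% at x = 10. So among two-session stoppers, having a rate at all may itself depend on the speed of adaptation. The percentages illustrate this and are not forecasts.

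**The case against.** The case on the other side has force and narrows the point.

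- The protocol states no exclusion of unfitted participants, and handling rules often sit in an SAP, which is not shown here. This stands as far as it goes, but no SAP can recover a rate from two points. It could only impute or change the analysis.
- The planned withdrawal of about 20% is general and is counted to the retention test. Someone lost after session 4 counts as withdrawn yet has all five training-phase points. The share lost within the first two of four consecutive days may be small. This stands.
- Section 3.2.1 reports similar adverse-event frequency and severity in RBT and control participants in earlier work, and says that very high intensity perturbations will be avoided. Unequal loss is therefore possible, not established.
- Section 1.2 requires an optimal intensity to show no apparent negative consequences, and adverse outcomes are compared between groups. That would make intolerance visible, but it does not repair the learning-rate contrast.

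Three stronger readings are tempting, and the protocol does not support them.

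- *The comparison is made only among people who tolerated their assigned intensity.* Participants with modified training stay in, three-session participants can be fitted, a two-session fit sometimes exists, people may leave for unrelated reasons, and nothing says that stopping training ends assessment.
- *The bias favours high intensity.* That needs intolerance to go with slow adaptation, and no section links them.
- *The bias can be sized by cutting the slow tail from a normal distribution with SD 9.7.* Such a distribution puts about 48% of values below zero at a mean of 0.4 (Φ(−0.4/9.7)) and about 42% at a mean of 2 (Φ(−2/9.7)). A positive time constant with mean 0.4 cannot have its mean lowered by more than 0.4.

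**Conclusion.** The point holds in a limited form. As the endpoint is constructed, and with baseline in the fit, stopping after session 1 leaves no identifiable learning rate and stopping after session 2 leaves an exact fit at best. If baseline is left out, neither has a unique rate. The primary comparison thus tends to omit randomised people with measured step counts, and the protocol's remarks on tolerance and withdrawal make unequal omission by group plausible.

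The size of the effect is unknown. It depends on how many people stop within two sessions, how they divide between groups, and whether stopping is related to adaptation. The protocol gives none of these. The conclusion rests on the count of points against parameters and assumes that a missed session means a missed test. It does not rest on any assumed distribution of x.

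**What to change.** In section 2.7, add a pre-specified repeated-measures (mixed) model of the baseline and session-end step averages, with group, time, group-by-time and sex. Include every randomised participant with a baseline and at least one session-end test. Estimate the two contrasts already planned, high against moderate and RBT combined against walking, in the change over sessions.

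State that hypotheses 1 and 2 will be read from the learning-rate ANCOVA only together with this model. Report by group how many participants had no fitted rate.

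This needs no new data, and section 2.8.1 already names the number of steps as the primary outcome. The cost is some extra analysis and a contrast in steps, not in time-constant units. The model uses early stoppers' observed points but still assumes that later missing values are explained by what was observed. It reduces the selection problem and cannot guarantee its removal. The wording should be settled before outcome data are seen.

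### The primary endpoint, a time constant x fitted separately to each participant's few averaged points, is not identified for non-learners and barely estimable at 0.4 and 10, so the comparison of raw x depends on fitting limits

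*Protocol*

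**What the plan says.** Section 2.8.1 of the Protocol gives the endpoint: "We will calculate the learning rate for each participant by fitting an exponential function". The data for each fit are the "average number of steps taken at each assessment time point". The curve is a + b·exp(−t/x), with x called the learning rate. Each average rests on three trials: "Participants will experience 3 forward-directed platform translations".

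Section 2.7 fixes the test: "One-way analysis of covariance (ANCOVA), with sex as a covariate, will be used to compare learning rates between the 3 groups", at alpha 0.05. Section 2.6 powers the trial on mean x of 0.4, 2 and 10 (high-intensity, moderate-intensity, walking control) with one SD of 9.7.

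Two other passages bear on what is measured and when. Section 1.2 says the team will "calculate the rate of decline in average number of steps taken to recover balance (i.e., learning rate". Section 2.1 places the stepping tests before training, "at the end of each training session (to determine the rate of adaptation), and after a delay of one week". Section 2.8.1 lists the tests this way: "Responses to backward-fall perturbations will be assessed at the end of each session, and at the one-week retention time-point".

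**The concern.** Hypotheses 1 and 2 both rest on x. A three-parameter curve on five coarse points gives a usable x only when the bend of the curve falls inside the observation window and is large relative to the noise. Two of the three planning values put the bend outside that window, and a participant who does not improve has no bend at all. Any x recorded for such a person comes from the fitting routine's limit or starting value. ANCOVA on raw x then gives those values full weight, and the largest dominate means and variances.

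Two further features add to this. x carries no information on how much a participant improved. The text also leaves open whether the one-week retention test enters the fit.

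**Working it through.** **The plan's own figure.** The mean of 0.4, 2 and 10 is 4.133. Squared deviations are 13.94 + 4.55 + 34.42 = 52.91. Δ = 52.91 / 9.7² = 52.91 / 94.09 = 0.562, and 9.64 / 0.562 = 17.1 per group. The Protocol's 0.56 and 17 reproduce, so the fault is in the endpoint and not in this arithmetic.

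**Data per fit.** One pre-training test plus four sessions gives 5 averages for 3 parameters. Averages of three integers move in steps of 1/3 = 0.33. Section 2.6 expects a fall from 3–4 steps to 1–2, so b is taken as about 2.

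**No improvement (b = 0).** The curve reduces to the constant a, and x drops out. This is algebra and needs no noise assumption.

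**x = 0.4.** 1 − exp(−1/0.4) = 0.918. After session 1 only 2 × 0.082 = 0.16 step of change remains, about half the 0.33-step resolution. Smaller values of x look almost the same.

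**x = 10.** 1 − exp(−4/10) = 0.330, so a third of the curve is seen. With b = 2, b·exp(−t/10) at t = 0 to 4 is 2.000, 1.810, 1.637, 1.482, 1.341. The least-squares line 1.983 − 0.165t misses by at most 0.017 step, so a, b and x cannot be separated.

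**x = 2.** The bend lies inside the window. Simulated medians were 1.8–2.0, but with five points 7–31% of fits sat on a limit.

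**Simulation.** Assumptions not in the Protocol: steps falling from 3.5 towards 1.5, rounded counts with a floor of 1, trial SD 0.3–0.8, least squares with x searched from 0.05 up to a stated limit.
- True x = 0.4: 21–41% of fits on the lower limit.
- True x = 10: 32–46% on the upper limit.
- Flat participant: 24–35% on the lower limit (read as fastest learning) and 22–38% on the upper.

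With five points, trial SD 0.5, 17 per group and control x = 10:

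| Upper limit | Control mean of x | Pooled SD |
|---|---|---|
| 20 | 9.4 | 6.6 |
| 30 | 13.7 | 10.1 |
| 100 | 43.8 | 34.7 |
| 1000 | 430.6 | 352.3 |

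**Power.** For high versus moderate intensity on x, five-point runs without between-person variation gave 29–99%. Runs with between-person variation gave 6–54% in one set and 39–94% in another. The error term also matters: pooling over all three groups brings in the control group's large variance and lowers power. Mean steps over sessions 1–4 minus baseline gave 79–100% in the first runs and 66–92% in the set with 6–54%. Omnibus power on x was 68–100% in the first runs, which covered five and six points.

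**Common SD.** 9.7 / 0.4 = 24 and 9.7 / 2 = 4.9 times the group mean. With fitting limits of 20–100, the simulated SD was 0.9–11 in the high-intensity group and 9–49 in controls.

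**Size of improvement.** A control who goes from 3.5 to 3.2 steps in one session and then stays there has x near its lower limit. A trainee with a = 1.25, b = 2.25 and x = 2 goes from 3.5 to 1.25 + 2.25·exp(−2) = 1.55, yet scores as slower.

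**Day 12.** Add a sixth point equal to the session 4 value (perfect retention, no noise) and refit. A true x of 10 becomes about 4.0 if the test is coded t = 5, or 2.3 if coded by day as t = 11. A true x of 2 becomes 1.78 or 1.57.

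**The case against.** Much can be said for the plan, and several stronger readings fail.

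- A reader might infer that x is unestimable at every planning value, or that the test is empty. Neither follows. x = 2 can be estimated, and omnibus power stayed high in most settings (about 51% at trial SD 1.2 with a limit of 30). Much of that signal, though, comes from how often fits hit a limit.
- A reader might take b = 0 as the expected control result. The Protocol assumes x = 10, a partial decline, and controls meet the test perturbation at every session. Non-learners are a risk and not the stated expectation.
- An SD of 9.7 around a mean of 0.4 is not impossible. It requires extreme skew, and the Protocol does not constrain x to be positive.
- The Protocol does not say that Day 12 enters the fit. Section 2.1 ties adaptation rate to the sessions, and only the wording in section 2.8.1 is open.
- Low power for hypothesis 1 does not itself prove an estimation fault. The plan's own inputs give 1.6 / (9.7·√(2/17)) = 0.48 standard errors, about 8% power. That is a separate sample-size matter.
- The direction of x is clear from the planning values, and section 2.7 tests average steps separately as a secondary outcome.
- Fitting limits and rules for flat data may stand in an analysis plan not shown here. Their absence is no finding. Limits can tidy the output, but they cannot make x identifiable.

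**Conclusion.** The concern holds for non-learners and for the extreme planning values. The result at b = 0, the 92% at x = 0.4 and the 0.017-step gap at x = 10 (for b = 2) follow from the stated formula and schedule. The dependence on fitting limits is shown by simulation: the control mean of x goes from about 10 to about 45 as the upper limit goes from 20 to 100. Hypothesis 1 power runs from under 10% to over 90% across limits, noise levels and simulation set-ups. Those sizes rest on assumed trial noise and between-person variation, so they are a range and not a forecast. Limits near 30 give a pooled SD close to the pilot 9.7.

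One common SD of 9.7 is implausible and points to heavy skew and unequal variance, which suits an untransformed ANCOVA badly. x is a time constant that ignores the size of improvement, whereas section 1.2 describes a rate of decline in steps. Whether Day 12 enters the fit needs one clear sentence. The endpoint and its test are fixed in the Protocol, so this should be corrected before analysis.

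**What to change.** Make the primary test of hypotheses 1 and 2 a mixed model of step counts at the end of sessions 1–4, with group, session, group × session, baseline steps and sex. Put the planned contrasts on the early-session or session-averaged difference, and report x descriptively.

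Alternatively, keep the learning-rate estimand but estimate it for all participants together in one nonlinear mixed model on log(x).

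In either case:
- state that only baseline and sessions 1–4 enter, and that Day 12 serves retention alone;
- label x a time constant, smaller meaning faster;
- re-run the power calculation on the pilot step counts.

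The cost is revised wording and a new power calculation, with no new data. The drawback of the first option is that a session-averaged difference mixes speed with size of improvement. Section 1.2 asks about improvement in fewer sessions, so an early-session contrast stays closer to that question.
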